### Test procedure

Participants will be sent a study information sheet at least 24 h before their first test session. At the first test session, participants will provide signed informed consent. All testing will be carried out at the NIHR Nottingham Hearing Biomedical Research Unit. Audiometric testing will be performed in double walled sound attenuating booth. Speech perception and cognitive testing will take place in a quiet, purpose-designed test room. Auditory stimuli will be presented in the free field via a single speaker (Genelec Inc., MA) situated directly in front of the participant at their most comfortable loudness (MCL) level [40].

Cogmed RM working memory training will be delivered via the internet at the participant’s home, using either their home PC or a laptop loaned by the NIHR Nottingham Hearing Biomedical Research Unit. Auditory elements will be presented in the free field using built-in or portable speakers at participants’ MCL. Training will be home-based with telephone monitoring once per week to ensure progress is maintained and to monitor for any practical or technical issues with training. Participants will be supported throughout their at-home training by a training aide, typically their spouse, who will offer support and guidance in accordance with Cogmed guidelines. Training aides will be instructed on their role by a qualified training coach at the NIHR Nottingham Hearing Biomedical Research Unit.

#### Blinding of participants

Participants will be blind to group allocation and it will not be possible for participants to tell from the online training interface which group they have been assigned to.

#### Blinding of tester

The researcher responsible for testing participants at baseline and post-intervention outcome assessments will not be involved in the allocation of participant IDs and will be blind to participants’ group allocation.

### Intervention

Cogmed RM working memory training (Figure 2) consists of 11 different sequence-based verbal and visuospatial working memory and memory storage games (Table 1). Participants are required to complete 25 sessions over 5 weeks (5 sessions per week), actively training for 35 to 45 minutes a day.

**Figure 2 F2:**
[figure not shown]
User home screen for working memory training.

**Table 1 T1:** Working memory training tasks

**Training tasks**	**Task type**
Asteroid, sorter, 3D cube, rotating data link	Visuospatial working memory
Input module with lid	Verbal working memory
Input module, stabilizer	Visuospatial and verbal working memory
Data room, visual data link, space whack	Visuospatial storage
Decoder	Verbal storage

#### Adaptive training

For the experimental group, training task difficulty (number of to-be-remembered items) is adaptive, based on individual performance, to maintain average daily performance levels of approximately 60% of trials correct.

#### Non-adaptive training

For the active control group, non-adaptive training tasks are fixed at a low-difficulty practice level (three to-be-remembered items) and task difficulty will not increase for the duration of the training.

### Data management

The chief investigator is the data custodian. This study will abide by the Caldicott principles. Data will be stored in accordance with NHS guidelines.

Data collected on paper will be entered onto a database accessible only by the research team and stored alongside electronic data. The database will be password protected and held on the NIHR Nottingham Hearing Biomedical Research Unit network, which is also protected with a password that is changed every 12 months. Paper files will be stored in filing cabinets in a locked room. All identifiable files will be stored separately from data. Data will carry a unique (non-identifiable) study number. Electronic data is backed up daily, with backup files stored off site in a fireproof cabinet. Only the primary investigator, chief investigator, and the unit statistician will have access to the final data set.

### Data analysis and statistical methods

Analyses will be performed to include those of the 62 recruited participants who meet the study criteria and complete the trial. Any participant leaving the study before its completion will not be replaced. Missing data will be accounted for using a method of multiple imputation (replaced with plausible values based on Monte Carlo-simulated data points from the data set). Effect sizes will be calculated using Cohen’s *d*, using the pooled standard deviation of the two groups.

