## Methods/Design

The study is a single-center, phase II, double-blind, randomized, active controlled trial, with minimized allocation of participants to one of two groups (Figure 1). One group (experimental) will receive adaptive working memory training, where task difficulty adjusts according to individual participant performance. The second group (active control) will receive non-adaptive training, fixed at low-difficulty practice level (3 to-be-remembered items). The use of an active control group for comparison will help account for any placebo effects, thus increasing confidence in the estimation of effect in the adaptively trained group that improvements in outcomes result from the development of working memory ability (as trained using an adaptive training program), rather than simply the provision of a the training program *per se*. The research edition of Cogmed RM working memory training will be used as this has been designed for double-blind randomized active controlled trials and provides no indication to either participants or testers of which training group (experimental or active control) a participant has been allocated.

One initial assessment and two baseline sessions, conducted a maximum of 1 week apart (T1 and T2), will be completed prior to allocation of training. The two baseline sessions will help account for any improvements in outcomes as a result of test-retest effects (procedural learning) prior to the intervention, thus increasing our confidence in the estimation of subsequent intervention-specific effects.

Working memory training will be delivered in participants’ homes via an online training portal. Participants will complete a total of 25 sessions (5 sessions per week for 5 weeks). Improvements for trained tasks will be assessed using the Cogmed ‘index of improvement’. Following training, participants will return for a post-intervention outcome assessment at T3. Participants in the active control group who receive the non-adaptive training will be unblinded following their T3 assessment and offered the adaptive training. Participants in the experimental group will remain blinded at T3 and will be invited to return for a 6-month follow-up assessment at T4 (31 weeks) to assess retention of any post-training improvements in outcomes (Figure 1).

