### Efficacy analyses

The primary endpoint and first analysis of group data will take place at the end of the 7-week randomized controlled trial (week 7). Repeated measures analysis of variance (ANOVA) will be used to assess any main effects of time and training group (experimental vs. active control) on the primary and secondary outcome measures. In addition, exploration of any significant interaction effects will enable the identification of whether Cogmed (adaptive) training for participants in the experimental group results in significantly different outcome performance than Cogmed (fixed) training for participants in the active control group. The mean difference in the primary outcome measure (Visual Letter Monitoring Task) for the main intervention assessment comparison (T2-T3) will be presented as a mean difference and 95% confidence interval (CI) for each of the two groups. Within-group and between-group comparisons for the primary and secondary outcome measures will be conducted using paired and independent t tests (or non-parametric equivalents). Pearson’s product moment (or Spearman’s rho correlations) will be used to identify relationships between improvements in behavioral performance of speech perception and cognition and improvements in self-reported hearing ability, to help inform clinically significant benefits for people with hearing loss.

The second endpoint and planned analysis will take place at the end of T4 (week 31), for the experimental group only, to examine the retention of any post-training improvements in the primary and secondary outcomes at a 6-month follow-up assessment. Repeated measures ANOVA will be used to assess any main effects of time the primary and secondary outcome measures for participants in the experimental group. The mean difference in the primary outcome measure (Visual Letter Monitoring Task) for the main retention assessment comparison (T3-T4) will be presented as a mean difference and 95% confidence interval (CI). Within-group comparisons for the primary and secondary outcome measures will be conducted using paired and independent t tests (or non-parametric equivalents).

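### The analysis set is limited to eligible completers with no analysis of all participants as allocated, and the plan does not say whether multiple imputation covers those who leave

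*Protocol article*

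**What the plan says.** Three consecutive sentences under Data analysis and statistical methods set the rule. The first defines who is analysed: "Analyses will be performed to include those of the 62 recruited participants who meet the study criteria and complete the trial". The second reads: "Any participant leaving the study before its completion will not be replaced". The third reads: "Missing data will be accounted for using a method of multiple imputation", with a short gloss on simulated plausible values and nothing on whose missing values are meant. The first sentence has no qualifier, so it governs the primary analysis as well as the others. Completion of the trial is not defined.

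On timing, Efficacy analyses states: "The primary endpoint and first analysis of group data will take place at the end of the 7-week randomized controlled trial (week 7"). Methods/Design gives the arms different last visits. Of the control arm it says that they "will be unblinded following their T3 assessment and offered the adaptive training". Of the other arm it says: "Participants in the experimental group will remain blinded at T3 and will be invited to return for a 6-month follow-up assessment at T4".

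The arms also train under different conditions. Difficulty in the experimental arm is adjusted "to maintain average daily performance levels of approximately 60% of trials correct", while the Non-adaptive training section fixes the control arm at three items throughout. The Power analysis section allows for attrition of no more than 15%.

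**The concern.** Minimisation balances the groups as they are allocated. It gives no such protection to the subset who finish, because finishing comes later and can be influenced by the training itself. One arm works near its limit for 25 sessions and the other repeats an easy task. The reasons for leaving, and the kind of participant who leaves, could therefore differ between arms. If they do, the completers are no longer comparable and the week-7 difference mixes a training effect with a selection effect.

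The imputation sentence does not clearly repair this. If leavers are already out, imputation can only fill isolated gaps among those who stayed. If leavers are meant to be in, the first sentence is wrong. One analyst could report roughly 53 completers and another all 62 with imputation, and both could claim to have followed the protocol. That choice should not remain open once outcome data exist.

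Restricting to those who meet the study criteria is harmless if eligibility is judged only on data from before allocation. The text does not say that it is.

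**Working it through.** **Inputs.** From the Power analysis section: target 1.5 words, pooled SD 2.118, one-sided 5% error, 80% power, 27 per group needed, attrition up to 15%, 31 per group recruited. Assumed here: 2.118 is the SD of the T2 to T3 change (the protocol says only that it is pooled), and informative loss occurs in one arm only.

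**The plan's own figure.** Normal approximation: n = 2 × [(1.645 + 0.842) × 2.118 / 1.5]² = 24.7, so 25 per group. The exact noncentral t gives 26. The stated 27 is within two of both, so the sample size is not at issue here.

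**How many are affected.** 31 × 0.15 = 4.65, so about 4 to 5 per arm. Expected completers are 31 × 0.85 = 26.4 per arm, or about 53 in total.

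**Moderate scenario.** Let q be the share lost in one arm and g the deficit of leavers against completers, in SD units. The mean of everyone allocated to that arm is (1 − q) × M + q × (M − g × SD), where M is the completer mean. The completer mean therefore exceeds it by q × g × SD.

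| q | g | Shift (words) | Share of 1.5 |
|---|---|---|---|
| 0.05 | 0.25 | 0.03 | 2% |
| 0.15 | 0.25 | 0.08 | 5% |
| 0.15 | 0.5 | 0.15 × 0.5 × 2.118 = 0.16 | 11% |
| 0.15 | 1.0 | 0.32 | 21% |
| 0.30 | 1.0 | 0.64 | 42% |

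The last row doubles the protocol's attrition figure and is shown only to mark the range.

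**Extreme scenario.** Suppose exactly the 4 lowest gainers of 31 leave. Removing the lowest fraction p of a normal distribution raises the mean by SD × φ(z_p) / (1 − p). With p = 4/31 = 0.129, z_p = −1.131 and φ = 0.2105, the shift is 2.118 × 0.2105 / 0.871 = 0.51 words, or 34% of the target. With 5 of 31 the result is 0.62, but 5/31 is 16.1%, above the protocol's own ceiling.

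**Direction.** A shift in the experimental arm inflates the difference. The same shift in the control arm shrinks it. Equal shifts in both cancel. The document gives no dropout figures by arm, so no sign can be assigned.

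**What imputation can recover.** A simulation removed the 4 lowest gainers of 31, with change SD 2.118 and an assumed common correlation of 0.5 to 0.7 between T1, T2 and T3. Completer bias was 0.49 words. Filling the missing T3 values by regression on T1 and T2 left 0.37 to 0.38. When loss depends on the unseen outcome, imputation removes only a part, and obtaining the T3 score matters more.

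**Power after the change.** Exact one-sided power for 1.5 words is 86.7% with all 31 per arm observed, and 80.9% to 82.2% with information equal to 26 to 27 per arm. No new sample size is needed.

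**The case against.** Four points can be made for the plan, and most of them limit the claim without removing it.

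*Imputation and a completer set can coexist.* The trial collects many tests over several visits, and a participant who finishes may still have a lost run or a skipped questionnaire. This stands. A reader might infer that the two rules contradict each other, but the text supports only that the scope of imputation is unstated.

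*Week 31 need not enter.* Because only the experimental arm has a T4 visit, a reader might infer that an experimental participant seen at T3 but lost before week 31 would be dropped from the primary analysis, while a similar control would be kept. Efficacy analyses speaks against this. It describes the randomised trial as lasting seven weeks and schedules the first group analysis then, before T4 attendance can be known. What remains is an undefined term.

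*The bias need not favour training.* A reader might infer an upward bias because adaptive training is demanding. Fixed, easy sessions could equally lose controls through boredom, and the weekly calls and training aide are described without distinction by arm. Completing the trial is also not the same as completing the training. This stands, and the direction is open.

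*This is a phase II trial seeking preliminary evidence.* That is true, but the article fixes the analysis population itself and does not leave it to another document. The trial also presents itself as offering high-level evidence.

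**Conclusion.** The concern holds in this form: every analysis, including the week-7 primary comparison, is restricted to eligible completers; no as-allocated analysis is stated; and the scope of imputation with respect to leavers is left open. With the attrition the protocol itself expects, the primary result depends on an event after allocation and can be biased either way.

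The size is illustrative. About 0.16 words (11% of the target) rests on 15% loss in one arm with leavers 0.5 SD worse. About 0.51 words (34%) is a worst case that requires precisely the four lowest gainers of one arm to leave. Both take 2.118 as the SD of change. If dropout is unrelated to gain, or acts equally in both arms, the bias is zero. The documents establish neither an outright contradiction with imputation, nor a difference between arms in the completion rule, nor an upward direction.

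**What to change.** Replace the sentence that defines the analysis set with wording to this effect:

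- The primary week-7 analysis includes all allocated participants, in the group to which they were allocated, whether or not they complete training.
- T3 assessments are sought from participants who stop training.
- Multiple imputation covers missing T3 values of leavers, and is done by arm using T1, T2 and the minimisation factors (age, sex, hearing aid type, baseline working memory).
- The completer set is kept as a sensitivity analysis.
- Completion is defined separately for week 7 and week 31, and T4 attendance has no bearing on inclusion at week 7.
- Any eligibility restriction rests only on data from before allocation.

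The second item does most to reduce bias, because imputation from T1 and T2 only partly corrects loss driven by the outcome. The cost is a change of wording and a few extra follow-up contacts. The estimate may be slightly diluted by participants who trained little.

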### Baseline characteristics

Baseline characteristics (including but not limited to; age, sex, hearing loss, working memory capacity, hearing aid use, hearing disability, hearing handicap, speech perception) will be described for each group.

### Efficacy analyses

The primary endpoint and first analysis of group data will take place at the end of the 7-week randomized controlled trial (week 7). Repeated measures analysis of variance (ANOVA) will be used to assess any main effects of time and training group (experimental vs. active control) on the primary and secondary outcome measures. In addition, exploration of any significant interaction effects will enable the identification of whether Cogmed (adaptive) training for participants in the experimental group results in significantly different outcome performance than Cogmed (fixed) training for participants in the active control group. The mean difference in the primary outcome measure (Visual Letter Monitoring Task) for the main intervention assessment comparison (T2-T3) will be presented as a mean difference and 95% confidence interval (CI) for each of the two groups. Within-group and between-group comparisons for the primary and secondary outcome measures will be conducted using paired and independent t tests (or non-parametric equivalents). Pearson’s product moment (or Spearman’s rho correlations) will be used to identify relationships between improvements in behavioral performance of speech perception and cognition and improvements in self-reported hearing ability, to help inform clinically significant benefits for people with hearing loss.

The second endpoint and planned analysis will take place at the end of T4 (week 31), for the experimental group only, to examine the retention of any post-training improvements in the primary and secondary outcomes at a 6-month follow-up assessment. Repeated measures ANOVA will be used to assess any main effects of time the primary and secondary outcome measures for participants in the experimental group. The mean difference in the primary outcome measure (Visual Letter Monitoring Task) for the main retention assessment comparison (T3-T4) will be presented as a mean difference and 95% confidence interval (CI). Within-group comparisons for the primary and secondary outcome measures will be conducted using paired and independent t tests (or non-parametric equivalents).

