### Research objective

Does working memory training result in improvements in cognition, speech perception and self-reported hearing abilities in adults with mild-to-moderate hearing loss who are existing hearing aid users, compared with an active control group (non-adaptive, placebo training)?

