### Outcome measures and power analysis

#### Primary outcome measure

Change in performance in an untrained measure of verbal working memory (Visual Letter Monitoring Task) will be the primary measure of efficacy in the present study. The Visual Letter Monitoring Task [32] is a visual measure of verbal working memory updating that is not trained within the Cogmed package. There are 10 consonant-vowel-consonant (CVC) words embedded in an 80-letter sequence. Two sequences will be presented to participants at each visit in counterbalanced order. Individual letters are displayed sequentially on a computer screen at a rate of 2 s per letter (first list) and 1 s per letter (second list). Participants will be asked to press the keyboard ‘space bar’ (hit) when three consecutive letters formed a recognized CVC word (for example, M-A-T). The test provides two measures, total number of hits (maximum score of ten per list) and d’ (d prime).

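### The only week-7 primary-outcome estimate promised with a confidence interval is each arm's own T2-T3 change; the planned between-arm comparison has no interval and is not named as primary

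*Protocol article*

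**What the plan says.** The Research objective asks whether working memory training improves outcomes "compared with an active control group (non-adaptive, placebo training"). The hypothesis likewise expects larger gains with adaptive than with non-adaptive training. Under Primary outcome measure, "Change in performance in an untrained measure of verbal working memory (Visual Letter Monitoring Task) will be the primary measure of efficacy".

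Efficacy analyses then sets out four elements for week 7:

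- A repeated measures ANOVA, "used to assess any main effects of time and training group (experimental vs. active control").
- The interaction, introduced second: "exploration of any significant interaction effects will enable the identification of whether Cogmed (adaptive) training" leads to a different outcome from the fixed version.
- The estimate. The mean difference in the primary outcome "for the main intervention assessment comparison (T2-T3") "will be presented as a mean difference and 95% confidence interval (CI) for each of the two groups".
- The tests. "Within-group and between-group comparisons for the primary and secondary outcome measures will be conducted using paired and independent t tests", or non-parametric equivalents.

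Data analysis and statistical methods adds Cohen's d, "using the pooled standard deviation of the two groups". It names neither the contrast nor an interval.

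**The concern.** The article fixes which quantity gets a point estimate and a 95% CI for the primary outcome, and that quantity is the pre-post change in each arm separately. This does not answer the trial's question. The Methods/Design section explains that the active control is there to account for placebo effects, and that two baseline sessions are there to account for test-retest learning. A within-arm T2-T3 change removes neither placebo response nor whatever practice effect remains after T2. Only the contrast between arms does so.

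The plan gives no order of importance. Paired within-arm tests and independent between-arm tests share one sentence. The ANOVA is described first by its main effects of time and group, neither of which isolates the difference in change. The interaction does isolate it, but is to be explored where significant. A report that follows this text could give two per-arm intervals and a set of p-values without showing how large the training effect is against control, or how precisely it is known. Readers would then tend to compare the two arms' separate results, which does not test a difference between them.

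**Working it through.** **Inputs.** From the Power analysis section: target 1.5 words, pooled SD 2.118, one-sided 5% type I error, 80% power, 27 per group. The document does not give an SD for the T2-T3 change. I assume 2.118 and show 1.5 and 3.0 as a range. The gain shared by both arms is also not given and is varied below.

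**1. Which contrast was the trial sized for?**

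- Two-sample, normal approximation: n per arm = 2 × [(1.645 + 0.842) × 2.118 / 1.5]² = 24.7, so 25.
- Two-sample t test: 25.4, so 26. Dividing 25.4 by 0.955 for a rank test gives 26.6, so 27.
- Within-arm paired t test with the same inputs: 13.8, so 14.

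The stated 27 fits a one-sided two-arm comparison (25 to 27). It does not fit a within-arm test (14).

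**2. Precision of the promised and the relevant interval** (27 per arm)

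- One arm's change: t(26) × SD/√27 = 2.056 × 0.408 = 0.84 words.
- Between-arm difference in change: t(52) × SD × √(2/27) = 2.007 × 0.576 = 1.16 words.

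| SD of change | Per-arm half-width | Between-arm half-width |
|---|---|---|
| 1.5 | 0.59 | 0.82 |
| 2.118 | 0.84 | 1.16 |
| 3.0 | 1.19 | 1.64 |

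The ratio is 1.38 whatever the SD.

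**3. What would happen if per-arm results were read as efficacy?** Suppose there is no training effect, both arms gain the same amount, and each arm has a two-sided 5% paired t test. Let p be the probability that an arm shows a significant gain and q the probability that it is significant in either direction, both from the noncentral t distribution with 26 degrees of freedom and noncentrality gain/(SD/√27). The arms are independent, so P(experimental shows a significant gain, control not significant) = p × (1 − q).

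At SD 2.118:

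| Shared gain (words) | p | Pattern probability |
|---|---|---|
| 0 | 0.025 | 2.4% |
| 0.4 | 0.155 | 13% |
| 0.6 | 0.294 | 21% |
| 0.8 | 0.472 | 25% |
| 1.0 | 0.656 | 23% |
| 1.5 | 0.943 | 5% |
| 2.0 | 0.997 | 0.3% |

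Over SDs of 1.5 to 3.0 and shared gains of 0.5 to 1.0 words, the range is about 8% to 25%. The ceiling is 25% because p × (1 − p) peaks at p = 0.5. For comparison, a valid between-arm test would err in this direction 2.5% of the time at two-sided 5%, or 5% of the time at the one-sided 5% used for the sample size.

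**The case against.** The strongest reply is that the between-arm question is already covered. The plan includes independent t tests for the primary and secondary outcomes. With time and group as factors, the interaction is the between-arm difference in change. Cohen's d with an SD pooled over two groups points to a between-group effect size. All of this stands, and a reader who inferred from the per-group sentence that no between-arm comparison is planned, or that no effect size will be shown, would be wrong.

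Second, a reader might infer that efficacy will be claimed when the experimental arm is significant and the control arm is not. The document states no such rule. Its hypothesis requires a greater improvement than in the control group. The 25% figure is therefore conditional on a misreading that the plan leaves open but does not adopt. It also depends on an unknown shared gain and falls to a few percent or less at the extremes. The extra baseline session may also make a large residual practice gain less likely.

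Third, calling T2-T3 the main comparison may only identify the visits, as the parallel wording for T3-T4 does. That is fair, and the label alone does not rank within-arm above between-arm evidence.

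Last, it can be said that the choice of which contrast to tabulate with an interval is a detail left to the full protocol or the SAP. This does not stand. The article is not silent here: it states the quantity to be presented, and that quantity is not the randomised contrast. That the missing interval follows directly from the planned independent t test makes the correction easy. It does not make the current sentence right.

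**Conclusion.** The point holds in a limited form. Between-arm tests are planned, but none is designated primary. The only week-7 primary-outcome estimate promised with a 95% CI is each arm's own change, and within-arm paired tests are listed alongside the between-arm tests as efficacy analyses. This conflicts with the research question, with the hypothesis and with a sample size that reproduces only as a two-arm comparison.

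The promised intervals would be narrower than the relevant one by a factor of 1.38: about ±0.84 against ±1.16 words, for a target effect of 1.5 words. The factor does not depend on the SD, but the widths rest on the assumed SD of change of 2.118 and 27 completers per arm. The false-positive figure, at most about 25%, applies only if per-arm results are taken as proof of efficacy, so it measures the risk of misreading and is not the plan's error rate.

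**What to change.** Replace the per-group sentence under Efficacy analyses with: 'The primary result is the between-group difference (experimental minus active control) in the Visual Letter Monitoring Task at T3, adjusted for the T2 baseline value, with its 95% CI. Per-group changes are descriptive, and within-group paired tests are not used as evidence of efficacy.'

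The between-group difference in T2-T3 change, with its CI, is an acceptable alternative. It has the same target and stays closer to the protocol's definition of the outcome as change. Either way, one of the two should be named as primary in advance. Apply the same rule to the week-7 secondary outcomes.

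The cost is wording only. It needs no new data, visits or participants, and the Trial status section describes the trial as still recruiting.
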